## Abstract

**Background:**

Multiresistant bacteria (MRB) is an increasing problem. Early identification of patients with MRB is mandatory to avoid transmission and to target the antibiotic treatment. The emergency department (ED) is a key player in the early identification of patients who are colonized with MRB.

There is currently sparse knowledge of both prevalence and risk factors for colonization with MRSA, ESBL, VRE, CPE and CD in acutely admitted patients in Western European countries including Denmark. To develop evidence-based screening tools for identifying carriers of resistant bacteria among acutely admitted patients, systematic collection of information on risk factors and exposures is required. Since a geographical variation is suspected, it is desirable to include emergency departments across the country.

The aim of this project is to provide a comprehensive overview of prevalence and risk factors for MRSA, ESBL, VRE, CPE and CD colonization in patients admitted to Danish ED’s. The objectives are to describe the prevalence and demography of resistance, co-infections, to identify risk factors for carrier state and to develop and validate a screening tool for identification of carriers.

**Methods:**

Multicenter descriptive and analytic cross-sectional survey from January–May 2018 of around 10.000 acutely admitted patients > 18 years in 8 EDs for carrier state and risk factors for antibiotic resistant bacteria. Information about the background and possible risk factors for carrier status together with swabs from the nose, throat and rectum is collected and analyzed for MRSA, ESBL, VRE, CPE and CD. The prevalence of the resistant bacteria are calculated at hospital level, regional level and national level and described with relation to residency, sex, age and risk factors. A screening model for identification of carrier stage of resistant bacteria is developed and validated.

**Discussion:**

The study will provide the prevalence of colonized patients with resistant bacteria on arrival to the ED and variation in demographic patterns, and will develop a clinical tool to identify certain risk groups. This will enable the clinician to target antibiotic treatments and to reduce the in-hospital spreading of resistant bacteria. This knowledge is important for implementing and evaluating antimicrobial stewardships, screening and infection control strategies.

**Trial registration:**

Clinicaltrials.gov: NCT03352167 (registration date: 20. November 2017).

## Background

Multiresistant bacteria (MRB) is an increasing problem in many parts of the world [1]. In Denmark, attention has been focused in particular to methicillin resistant *Staphylococcus aureus* (MRSA), but there has also been an increase in the prevalence of extended-spectrum beta-lactamase-producing enterobacteria (ESBL), vancomycin resistant enterococci (VRE) and carbapenem resistant enterobacteria (CPE) [2].

The consequences of the widespread antibiotic use and thus increasing bacterial resistance to antibiotics are multiple [3]. Both antibiotic-associated diarrhea caused by infections with toxin-producing *Clostridium difficile* (CD) [4] and infections and spread of MRB lead to increased healthcare costs, increased morbidity and mortality [5], and complicate advanced treatments that depend on effective infection control, like treatment of malignancies and transplantations [6, 7].

Early identification of patients colonized with resistant bacteria is mandatory to avoid in-hospital transmission and to target the antibiotic treatment to the individual patient. Antibiotics are used in many areas of the hospitals, but especially the treatment of acutely admitted patients often includes an antibiotic prescription. The emergency departments (ED) are key players in the in-hospital use of antibiotics and in the early identification of patients who are colonized with MRB since the majority of patients are admitted through these departments.

There is currently very sparse knowledge of both prevalence and risk factors for colonization with MRSA, ESBL, VRE, CPE and CD in acutely admitted, unselected patients in Western Europe countries including Denmark. A Danish study has shown that the prevalence of MRSA in an area with ​​presumed high numbers of carriers was 0.9% in the emergency department [8]. The prevalence of the other MRB has yet to be described at the ED level.

The Danish National Board of Health has published guidelines for targeted screening for isolation of MRSA, based on questionnaires concerning exposure factors [9]. This screening is expected to identify only some of the carriers [8]. In order to clarify the extent of the problem and prioritize the preventive response to the spread of MRB, it is crucial to know the prevalence of these bacteria in unselected acutely admitted patients to the Danish EDs. To develop evidence-based screening tools for identifying carriers of resistant bacteria among the acutely admitted patients, systematic collection of information on risk factors and exposures is required. Since there is a certain geographical variation in prevalence of carriers, it is desirable to include emergency departments across the country.

### Aims and objectives

The aim of this project is to provide a comprehensive overview of prevalence and risk factors for MRSA, ESBL, VRE, CPE and CD colonization in patients admitted to Danish emergency departments at a national level.

The objectives are:I)To describe the prevalence of MRSA, ESBL, VRE, CPE and CD colonization in unselected, acutely admitted patients and the regional, urban/country and other demographic variations.II)To describe the occurrence of simultaneous patient colonization with two or more resistant bacteria (MRSA, ESBL, VRE, CPE and CD).III)To identify risk factors for colonization with MRSA, ESBL, VRE, CPE and CDIV)Based on the identified risk factors, to develop screening tools for identification of carriers.

## Methods

Participants, interventions, and outcomes.

### Trial design

Multicenter descriptive and analytic cross sectional survey of acutely admitted patients for risk factors and carriage of MRB.

### Study setting

The project takes place in emergency departments and departments of clinical microbiology at the university hospitals in Odense, Aarhus, Aalborg, and Køge, and the regional hospitals in Aabenraa, Herning, Hjørring and Slagelse and covers 4 of the 5 Danish regions, and approximately 70% of the Danish population.

### Eligibility criteria

#### The inclusion criteria are

Patients aged 18 years or above.Patients present in one of the participating emergency departments at least 4 h.Patients must be mentally competent and able to consent to participate.

#### The exclusion criteria are

Patients who have been admitted for more than 16 h before enrollment.Patients where swabbing in the rectum, nose or throat is not possible due to anatomic or surgical reasons.

### Interventions

There are no interventions in this study.

### Outcomes

The primary outcome is the presence of MRB (MRSA, ESBL, VRE, CPE) and CD in patients in the ED, expressed as prevalence (proportion) in percentage on admission among the included patients.

The secondary outcomes are the information on admission concerning risk factors for carriage of antibiotic resistant bacteria, expressed as the proportion and odds ratios between patients with and without MRB (Table 1).

**Table 1 Tab1:** Variables examined in the study

Examined risk factors for carrying resistant bacteria	-Travel activity last year -Work/stay at hospital, nursing home, schools, prison, military, asylum center/refugee camp, hostel, daycare or war zone in and outside the Nordic region. -Signs of infections, shared sports equipment, tattoos/piercings -Contact with mink farm, live pigs, cattle or poultry -Hospitalized for the past six months -Invasive surgery performed at a foreign clinic/hospital -Drainage tubes, indwelling catheters, nutrition tubes, ulcers, abscesses, eczema, chronic skin disorders or IV drug abuse within the last six months -Antibiotic treatment within the last 6 months -Previously carrier of resistant bacteria, household-like contact with carrier or worked/stayed in places with known transmission of resistant bacteria
Outcome variables	-MRSA: methicillin resistant *Staphyloccus aureus* -ESBL: extended-spectrum beta-lactamase producing enterobacteria -VRE: vancomycin resistant enterococci (VRE) -CPE: carbapenem resistant enterobacteria -CD: *Clostridium difficile*

### Participant timeline

Enrolment to the study commences from January 2018. Due to local conditions some of the participating departments will include patients from February 2018. Enrollment continues until the predefined sample size for each department has been reached, which is estimated to be no longer than 4 months after the inclusion start in each department. The last patient is expected to be enrolled in the end of June 2018.

### Sample size

A Danish study showed an MRSA occurrence of 0.9% in an ED [8]. It is assumed that VRE and CPE have a lower occurrence and ESBL and CD a higher occurrence [2]. With the funding obtained, 1.325 patients can be included per ED, corresponding to 2650 patient in each region and 10.600 patients in total. The true frequencies of the prevalence of resistant bacteria with 95% confidence, based on expected prevalence of resistant bacteria of 0.5%, 1%, 10% and 25% is shown in Table 2 for different samples sizes (anticipated admission rate of 10.000 patients/year).

**Table 2 Tab2:** Sample size calculation for prevalence (source Openepi.com)

Calculations of sample size estimates 95% limits of confidence								
	sample size (number of patients)							
	600	1100	1500	1750	2200	3500	5000	10,000
Anticipated prevalence of resistant bacteria	95% limits of confidence (+/− % of prevalence)							
0.5%	+/− 0.5	+/− 0.4	+/− 0.35	+/− 0.30	+/− 0.25	+/− 0.20	+/− 0.14	+/− 0.03
1%	+/− 0.8	+/− 0.55	+/− 0.45	+/− 0.40	+/− 0.35	+/− 0.30	+/− 0.20	+/− 0.05
10%	+/− 2.5	+/− 1.75	+/− 1.4	+/− 1.25	+/− 1.2	+/− 1.0	+/− 0.6	+/− 0.2
25%	+/− 3.5	+/− 2.5	+/− 2.0	+/− 1.75	+/− 1.70	+/− 1.45	+/− 0.9	+/− 0.2
	Example: at a prevalence of for instance MRSA of 0.5% the 95% limits of confidence with a sample size of 1.100 patient is +/0.4%, which means that the prevalence with 95% certainty is from 0.1–0.9%.							

Assumptions: 10.000 patients pr year, 95% confidence limits

For the analysis of risk factors for carrier stage of resistant bacteria, only calculations at national level will be performed.

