### Data collection, management, and analysis

#### Data entry

All patients will be provided with project running number, which will be used throughout the project in the interviews and processing of microbiological samples to secure anonymity. An ID file with the project running number and the personal registration number (PRN) number will allow tracing the patient information concerning use of antibiotics before the admission in the national medicine registries, and for returning test answers to those patients who requested this information.

The answers from the interviews are entered directly to an electronic questionnaire (SurveyXact®, Rambøll, Aarhus, Denmark) on tablet PCs used solely for the project. Data is transmitted directly to the central secured data file storage.

The microbiological samples are analyzed anonymously using project running numbers and microbiological data are recorded in the local laboratory information system [Aarhus, Odense and Slagelse: MADS (Aarhus University Hospital, Aarhus, Denmark [www.madsonline.dk]) and Aalborg: ADBact (Autonik Ab, Sweden)]. Data is extracted from these databases after the end of the study to the central database where the results are merged to the interview information. The results will not appear in the patients hospital file.

Microbiological test results are merged with the interview data using the project running number and data from the medicine registries are merged with the data set by using the PRN number.

After data cleansing and validation the final data file will be anonymized before data analysis.

Information concerning antibiotic treatment before the admission will be obtained from National Board of Health, medicine registries.

The data analyzes are conducted in STATA 14 in cooperation with a statistician.

The prevalence of the resistant bacteria are calculated at hospital level, regional level and national level and described with relation to residency (region and degree of urbanization), sex, age and risk factors.

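### The worked example under Table 2 claims 0.1–0.9% with 95% certainty, but it rests on about 5.5 expected carriers; Wilson or exact limits are about 0.2–1.1%

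*Protocol article*

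**What the plan says.** All of this is in the protocol article.

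- **Planned numbers (Sample size).** Funding allows the following: "1.325 patients can be included per ED, corresponding to 2650 patient in each region and 10.600 patients in total".
- **Table 2 (Sample size).** It gives symmetric ± limits at four anticipated prevalences (0.5%, 1%, 10%, 25%) and eight sample sizes from 600 to 10,000. The source is an online calculator. The footnote reads "Assumptions: 10.000 patients pr year, 95% confidence limits".
- **Worked example (below Table 2).** It states that "at a prevalence of for instance MRSA of 0.5% the 95% limits of confidence with a sample size of 1.100 patient is +/0.4" per cent, "which means that the prevalence with 95% certainty is from 0.1–0.9" per cent.
- **Which organisms are rare (Sample size).** MRSA was 0.9% in an earlier Danish ED study. For the others, "It is assumed that VRE and CPE have a lower occurrence and ESBL and CD a higher occurrence".
- **Reporting levels (Data entry).** "The prevalence of the resistant bacteria are calculated at hospital level, regional level and national level".

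**The concern.** A symmetric interval for a proportion relies on the number of positives being large enough for the count to be roughly normal. The example has 5.5 expected positives. At that count the binomial is right-skewed and the estimated standard error shrinks when the count happens to be low. The ± interval then tends to stop short of the true prevalence.

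Prevalence is the primary outcome, it is to be given per hospital, and two of the five organisms are assumed rarer than MRSA. Low counts are therefore an expected case at hospital level. A reader who takes the example at face value will think a single ED bounds a rare organism more tightly from above than it does. The printed interval ends exactly at the 0.9% that the section cites as its MRSA starting point, whereas limits suited to the count run past it.

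**Working it through.** **Inputs.** p = 0.5%, n = 1,100, printed ±0.4 (worked example); N = 10,000 (Table 2 footnote); hospital sample 1,325 (Sample size); z = 1.96.

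**1. Reproduce the printed figure.**

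- Without population correction: 1.96 × √(0.005 × 0.995 / 1,100) = 0.417 points.
- With the correction √((N − n)/(N − 1)) = √(8,900/9,999) = 0.943: 0.417 × 0.943 = 0.393 points.

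Both round to 0.4. The table as a whole follows the corrected form: at 0.5% it prints 0.30 for n = 1,750 (corrected 0.300, uncorrected 0.330) and 0.14 for n = 5,000 (0.138 against 0.196). Either way the example is a normal-approximation half-width.

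**2. Expected carriers.** 0.005 × 1,100 = 5.5. At the planned hospital size, 0.005 × 1,325 = 6.6.

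**3. Limits suited to that count.** Wilson at p = 0.005, n = 1,100, z² = 3.84:

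- centre = (0.005 + 3.84/2,200) / (1 + 3.84/1,100) = 0.00672
- half-width = 1.96 × √(0.004975/1,100 + 3.84/(4 × 1,100²)) / (1 + 3.84/1,100) = 0.00450
- limits = 0.22% to 1.12%

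| Carriers in 1,100 | Wilson | Clopper-Pearson | Exact hypergeometric, N = 10,000 |
|---|---|---|---|
| 5 | 0.19–1.06% | 0.15–1.06% | 0.17–1.02% |
| 6 | 0.25–1.19% | 0.20–1.18% | 0.22–1.14% |

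The upper limit is 1.0–1.2% under every method, against a printed 0.9%. At the centre of that range, 1.12 − 0.9 = 0.22 points.

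**4. Coverage of the ± interval at a true 0.5%.** At n = 1,100, two carriers give 0.182% with an upper limit of 0.43%, below the truth; three carriers give an upper limit of 0.58%. The interval therefore falls wholly below the truth when at most two carriers are found: 0.0040 + 0.0223 + 0.0615 = 8.8%. It falls wholly above in 0.4%. Coverage is 100 − 8.8 − 0.4 = 90.8%.

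| n | Uncorrected width, binomial | Wholly below truth | Corrected width, hypergeometric (N = 10,000) | Wholly below truth |
|---|---|---|---|---|
| 1,100 | 90.8% | 8.8% | 91.7% | 7.6% |
| 1,325 | 88.9% | 10.3% | 90.8% | 8.7% |

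The nominal figure for each side is 2.5%. The table's own population assumption does not remove the fault. Wilson covers 97.1% at 1,100 and 95.2% at 1,325 (binomial).

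**5. Where it fades.** Uncorrected binomial coverage is 94.4% at 1% with n = 1,325, 94.4% at 0.5% with the regional 2,650, and 94.8% at 0.5% with the national 10,600.

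**The case against.** **The printed ±0.4 is not a miscalculation.** True: step 1 reproduces it. What fails is the sentence attached to it, which claims a 95% level that the formula does not deliver at 5.5 carriers. Reading the sentence as the range in which the estimate should fall does not rescue it. The chance of 2 to 9 carriers in 1,100 at a true 0.5% is 92.0% (binomial) or 93.6% (hypergeometric, N = 10,000).

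**Nothing was sized on this table.** Also true. The sample was set by funding, so corrected limits change no sample size, outcome or comparison. That limits the weight of the point, but the precision statement on the primary outcome is still wrong as printed.

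**The final analysis need not use a ± interval.** This stands in full. A reader might infer that published hospital prevalences will carry these intervals, including a zero-width interval when no carrier is found. The article says only that prevalence is calculated at each level. It names no interval method, and an analysis plan may well do so.

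**Most low-prevalence cells are not this sparse.** A reader might infer that the whole 0.5% and 1% rows rest on a handful of carriers. Only three of the 16 cells have 3 to 6 (0.5% at 600 and 1,100; 1% at 600); the others have 7.5 to 100. Nor does coverage fail at hospital level in general. At the cited MRSA figure of 0.9% with n = 1,325, uncorrected coverage is 94.2%, against 94.4% for Wilson. Coverage is saw-toothed in n and p, so isolated poor values should not be generalised.

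**A bigger problem sits in the same rows.** At 0.5% and n = 10,000 the table prints ±0.03, where the uncorrected value is 0.138. That comes from the N = 10,000 population correction, not from small counts. It is a separate and larger fault in the large-n columns, and correcting for skewness does not repair it.

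**Conclusion.** The point holds for the worked example and the low-count cells of Table 2. The stated 0.1–0.9% should be about 0.2–1.1%, with the upper limit about 0.2 points too low. Actual coverage at a true 0.5% is about 91–92% at n = 1,100 and 89–91% at the planned 1,325, and nearly all misses lie below the truth. These figures assume simple random sampling within a hospital, either from a very large population or from the table's N = 10,000; the conclusion is the same under both.

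It does not extend to the 10% and 25% rows, and it bears much less on the 1% row at hospital size or on the regional and national samples. It says nothing established about the intervals in the final report. It is a modest correction to stated precision on the primary outcome and does not affect the design.

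**What to change.** 1. Restate the worked example as about 0.2–1.1%.
2. In the low-count cells, replace ± with asymmetric Wilson or Clopper-Pearson lower and upper limits. Wilson values without population correction, beside what the printed ± implies:

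| Prevalence | n | Printed ± implies | Wilson |
|---|---|---|---|
| 0.5% | 600 | 0.0–1.0% | 0.17–1.46% |
| 0.5% | 1,100 | 0.1–0.9% | 0.22–1.12% |
| 0.5% | 1,500 | 0.15–0.85% | 0.25–1.00% |
| 0.5% | 1,750 | 0.20–0.80% | 0.26–0.96% |
| 1% | 600 | 0.2–1.8% | 0.46–2.16% |
| 1% | 1,100 | 0.45–1.55% | 0.56–1.78% |

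Where to stop along each row is a judgement. Using the same method throughout both rows would avoid having to choose.

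3. As a recommendation only, use the same type of interval for hospital-level prevalences of the rare organisms, if the analysis plan does not already say so.

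The cost is one sentence and six cells, with no extra patients and no design change. The only downside is a slightly less favourable stated upper limit.

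### Table 2 appears to treat 10,000 patients as the whole population, so its n = 10,000 precision is about 3 to 4.6 times too narrow for a study enrolling 10,600

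*Protocol article*

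**What the plan says.** The Sample size section of the protocol article ties enrolment to funding: "1.325 patients can be included per ED, corresponding to 2650 patient in each region and 10.600 patients in total". Precision is then shown in Table 2, captioned "Sample size calculation for prevalence (source Openepi.com", for eight sample sizes from 600 to 10,000, "based on expected prevalence of resistant bacteria of 0.5%, 1%, 10% and 25" per cent. The text adds in parentheses "anticipated admission rate of 10.000 patients/year", and a note under the table repeats it: "Assumptions: 10.000 patients pr year, 95% confidence limits". Neither place says whether the 10,000 is per department or in total.

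The n = 5,000 column reads ±0.14, 0.20, 0.6 and 0.9. The n = 10,000 column reads ±0.03, 0.05, 0.2 and 0.2. A worked example states that "at a prevalence of for instance MRSA of 0.5% the 95% limits of confidence with a sample size of 1.100 patient is +/0.4" per cent, "which means that the prevalence with 95% certainty is from 0.1–0.9" per cent, so the entries are absolute percentage points.

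Aims and objectives sets the target of inference as patients admitted to Danish emergency departments at national level. Study setting lists eight hospitals in four of the five regions, covering about 70% of the population.

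**The concern.** The table looks wrong before any formula is applied. Doubling a simple random sample should narrow the interval by √2 = 1.41. Between n = 5,000 and n = 10,000 the printed widths shrink by 0.14/0.03 = 4.7, 0.20/0.05 = 4.0, 0.6/0.2 = 3.0 and 0.9/0.2 = 4.5. The last column also gives ±0.2 for both 10% and 25% prevalence, although those widths should differ by √(0.1875/0.09) = 1.44.

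The likely cause is that 10,000 patients a year was entered as a population size, so that a sample of 10,000 counts as almost everyone. That cannot describe a study that enrols 10,600 and generalises to national admissions.

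Table 2 is the article's only statement of precision for the primary outcome, and its last column is the one nearest the national sample. A reader would expect national prevalence of a rare organism to within a few hundredths of a percentage point.

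**Working it through.** **Inputs.** From Sample size and Table 2: 95% confidence (z = 1.96); prevalences p of 0.5%, 1%, 10% and 25%; 10,000 patients a year; planned sizes of 1,325 per department, 2,650 per region and 10,600 in total. Assumption for a sensitivity check: if the 10,000 is per department, eight departments give N = 80,000.

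**Formulas.**
- Uncorrected half-width: d = z·√[p(1−p)/n].
- With finite-population correction: d = z·√[p(1−p)/n × (N−n)/(N−1)].
- Inverse: n = N·p(1−p) / [(d²/z²)(N−1) + p(1−p)].

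**Step 1: which formula produced the table?** At n = 5,000 and N = 10,000 the correction factor is √(5,000/9,999) = 0.707.

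| n = 5,000 | 0.5% | 1% | 10% | 25% |
|---|---|---|---|---|
| Printed | 0.14 | 0.20 | 0.6 | 0.9 |
| Corrected, N = 10,000 | 0.138 | 0.195 | 0.588 | 0.849 |
| Uncorrected | 0.196 | 0.276 | 0.832 | 1.200 |

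The corrected values agree with the printed ones to within rounding (0.849 against 0.9 at one decimal is the loosest). The uncorrected ones do not, by factors of 1.40, 1.38, 1.39 and 1.33.

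**Step 2: the n = 10,000 column.**

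| n = 10,000 | 0.5% | 1% | 10% | 25% |
|---|---|---|---|---|
| Printed | 0.03 | 0.05 | 0.2 | 0.2 |
| Corrected, N = 10,000 | 0 | 0 | 0 | 0 |
| Corrected, N = 10,600 | 0.033 | 0.046 | 0.140 | 0.202 |
| Corrected, N = 80,000 | 0.129 | 0.182 | 0.550 | 0.794 |
| Uncorrected | 0.138 | 0.195 | 0.588 | 0.849 |
| Uncorrected ÷ printed | 4.61 | 3.90 | 2.94 | 4.24 |

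For example, at 0.5%: 1.96 × √(0.005 × 0.995/10,000) = 0.00138, or 0.138 points. The printed column is not exactly reproduced. Strict N = 10,000 gives zero width, and N = 10,600 fits three of the four cells after rounding. Entering the printed widths in the inverse formula with N = 10,000 returns n = 9,550, 9,383, 8,963 and 9,474, all close to the assumed population. Without the correction, ±0.03 at 0.5% needs n = 1.96² × 0.005 × 0.995/0.0003², about 212,000 patients.

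**Step 3: consistency within the table.** At n = 3,500 the 10% and 25% rows print 1.0 and 1.45. Uncorrected values are 0.99 and 1.43; corrected values with N = 10,000 are 0.80 and 1.16. The table therefore does not follow one formula throughout.

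**Step 4: planned sizes, uncorrected.** None of these is a column of Table 2.

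| n | 0.5% | 1% | 10% | 25% |
|---|---|---|---|---|
| 1,325 | 0.38 | 0.54 | 1.6 | 2.3 |
| 2,650 | 0.27 | 0.38 | 1.1 | 1.6 |
| 10,600 | 0.13 | 0.19 | 0.57 | 0.82 |

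Removing an N = 10,000 correction widens the interval by √(9,999/8,675) = 1.07 at 1,325 and √(9,999/7,350) = 1.17 at 2,650.

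**Step 5: worked example.** At n = 1,100 and 0.5%, the half-width is 0.393 corrected or 0.417 uncorrected, so ±0.4 is a fair normal-approximation figure. But 0.5% of 1,100 is 5.5 carriers. Exact (Clopper-Pearson) limits are 0.15% to 1.06% for 5 carriers and 0.20% to 1.18% for 6, so an upper limit of 0.9% is too low.

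**The case against.** The strongest reply is that little depends on the table. Enrolment was fixed by funding, the error does not make the sample inadequate, and published intervals will be calculated from the data. The article does not say that those intervals will carry a finite-population correction. This stands: the error is in the stated precision, not in the design.

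Second, the large error sits in one column. For n = 600 to 3,500 the uncorrected-to-printed ratios run only from 0.96 to 1.19, and these columns bracket the department and regional sizes. The table does not label the last column as national. All true, but that column is the one nearest the national total of 10,600.

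Third, the mechanism is inferred. No formula is named, and the last column is not exactly reproduced. That is conceded. The printed widths are wrong for a sample from a large population whatever produced them.

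Fourth, the 10,000 may be per department. The correction would then be coherent for a single department, and the clash with 10,600 becomes a mistake of units. With N = 80,000, however, the last column is still too narrow by factors of 2.75 to 4.3.

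Fifth, the worked example is right by its own method. The remaining fault is a symmetric interval on five or six events, which is a smaller and separate matter.

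**Conclusion.** The concern holds. The n = 10,000 column of Table 2 understates the 95% half-widths by factors of 2.9 to 4.6, and the n = 5,000 column by 1.3 to 1.4. At the planned 10,600 the design gives about ±0.13, 0.19, 0.57 and 0.82 points, not the ±0.03 to 0.2 printed at 10,000.

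The ratios use the printed values as they stand. Allowing for rounding of the printed figures, 0.588/0.25 = 2.4 to 0.849/0.15 = 5.7 bounds the range.

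The uncorrected widths assume simple random sampling. The Background expects geographical variation in carriage, so limits for the pooled national figure could be wider still. Attributing the error to a finite-population correction is an inference, supported by the assumption stated twice, the match at n = 5,000 and the collapse at n = 10,000. Department and regional precision is little affected, and the sample size remains adequate.

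**What to change.** Replace Table 2 with half-widths computed without a finite-population correction at 1,325, 2,650 and 10,600 patients, using the Step 4 values, and delete the 10,000-a-year assumption from the text and the table note.

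For the 0.5% and 1% rows give Wilson or exact limits in place of symmetric ones, choose one type and name it. For 53 carriers in 10,600 the limits are 0.38% to 0.65% (Wilson) or 0.375% to 0.654% (exact). For 7 in 1,325 they are 0.26% to 1.09% (Wilson) or 0.21% to 1.09% (exact). Restate the worked example the same way, and use the same interval type when rare-organism prevalences are reported.

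The cost is one replaced table and one corrected example. The stated precision becomes less favourable; enrolment does not change.
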